### Randomization and blinding procedures

2.20

The randomization will be generated on the site www.randomization.com^[49]^ by a researcher not involved in the patient recruitment or data collection. It will be performed as block randomization with a 1:1:1:1 allocation. Patients will be stratified by sex to ensure equal numbers of women and men in each group and randomly allocated to 1 of 4 groups (n = 36 per group): Photobiomodulation + TENS, Photobiomodulation, TENS, or Placebo. The concealed allocation will be performed in consecutively numbered opaque envelopes. The envelopes will be sealed, and they will be stored in a secure cabinet. Prior to initiation of treatment, the therapist responsible for the treatment will open the sealed envelope to know in which group the patient will be included. Patient and evaluator will be blinded throughout the treatment. The same researcher will not apply therapies and perform evaluations.

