**Materials and methods::**

This a 4-arm randomized placebo-controlled trial with patient and evaluator blinded. This study will be performed in Department of Physical Therapy at Federal University of São Carlos, São Carlos/SP, Brazil. One hundred and forty-four patients with chronic neck pain will be randomized into 4 groups: active photobiomodulation therapy with active electrical stimulation, active photobiomodulation therapy, active electrical stimulation, or placebo treatment. They will receive 10 sessions of treatment. Primary outcome: pain intensity (measured by pain numerical rating scale) posttreatment. Secondary outcomes: pain during movement, neck disability, range of motion, pressure pain threshold, temporal summation, conditioned pain modulation, depressive symptoms, pain catastrophizing, quality of life, analgesic intake, and global perceived effect at posttreatment (10 sessions). Pain intensity and global perceived effect will also be measured after 6 weeks randomization.

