### Ethical aspects and study design

2.1

This protocol study was written following the recommendations of Standard Protocol Items: Recommendations for Interventions Trials (SPIRIT) and this 4-arm randomized placebo-controlled superiority trial with patient and evaluator blinded to the allocation group will follow the guidelines recommended by Consolidated Standards of Reporting Trials (CONSORT). Figure 1 provides a flowchart of the study.

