### Procedures

2.6

Patients will work with 2 separate researchers, 1 serving as the evaluator and the other serving as a therapist. Both are physiotherapists. The patients will be evaluated before the treatment, after the treatment (10 sessions) and 6 weeks after randomization. On the first session, the evaluator will collect sociodemographic data, medical history, and data related to the study outcomes. Then, the therapist will give each patient 10 consecutive days of treatment, with the exception of weekends, after which they will be re-evaluated by the evaluator. After 6 weeks randomization the evaluator will be in contact by telephone to the patients for a follow-up evaluation. All data entry will be coded and double-entered into an Excel spreadsheet for analysis.

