#### Secondary outcomes

2.8.2

Pain intensity during movement; neck disability; cervical range of motion; pressure pain threshold (PPT); temporal summation (TS); conditioned pain modulation (CPM); depression symptoms; pain catastrophizing; quality of life; analgesic intake; and global perceived effect. Secondary outcomes will be measured at baseline and posttreatment (10 sessions). Pain intensity and global perceived effect will also be measured in contact by telephone after 6 weeks randomization.

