### Study blinding assessment

2.21

Assessment of the effectiveness of blinding will be performed after the conclusion of the posttreatment evaluation. The evaluator will answer whether he thinks that the application of photobiomodulation and electrical current was real, placebo, or he does not know. After that, the evaluator will ask the patient: “Do you think that the application of photobiomodulation was real, placebo, or did not know?” and “Do you think that the application of electrical current was real, placebo, or do you not know?” Their responses will be recorded and used to gauge the adequacy of subject and investigator blinding.

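### The evaluator hears each patient's guess about treatment before collecting the 6-week pain and global perceived effect ratings by telephone, an avoidable weakening of evaluator blinding for these two secondary outcomes

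*Protocol article*

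**What the plan says.** All references are to the protocol article.

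- **Extent of blinding.** Section 2.20 says "Patient and evaluator will be blinded throughout the treatment". Section 2.1 describes a "4-arm randomized placebo-controlled superiority trial with patient and evaluator blinded to the allocation group", and the abstract a "4-arm randomized placebo-controlled trial with patient and evaluator blinded". The last two set no time limit.
- **Blinding check.** Section 2.21 places it after the final treatment-phase assessment: "Assessment of the effectiveness of blinding will be performed after the conclusion of the posttreatment evaluation". The evaluator goes first: "The evaluator will answer whether he thinks that the application of photobiomodulation and electrical current was real, placebo, or he does not know". The patient's turn follows: "After that, the evaluator will ask the patient", with one question for each therapy.
- **Follow-up.** Section 2.6 says "After 6 weeks randomization the evaluator will be in contact by telephone to the patients for a follow-up evaluation". Section 2.8.2 names what is collected: "Pain intensity and global perceived effect will also be measured in contact by telephone after 6 weeks randomization".
- **Staff.** Section 2.6 describes two researchers, one evaluator and one therapist. Section 2.20 has the therapist open the allocation envelope and keeps treating and evaluating in separate hands.
- **Mode.** Section 2.9 has the patient give the pain score aloud. At 6 weeks both ratings are given over the telephone.

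**The concern.** The evaluator is blinded so that the person who takes the ratings has no view of what the patient received. Section 2.21 gives that person information bearing on exactly this question, patient by patient and therapy by therapy, while two outcomes are still to be collected. Both are subjective ratings spoken to an interviewer, so the wording, tone or prompting of the call can affect them.

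The patient's guess may carry information. Section 2.18 is not needed to see this; the description of TENS under section 2.7 is enough. Active TENS runs for 30 minutes at a clearly felt level with regular adjustment, whereas the sham delivers current for 45 seconds in total. Some patients may notice.

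What is at stake is the evidence on duration. The Introduction hypothesises that the combination may act faster or last longer. The 6-week call is the only assessment after the post-treatment visit, so whatever the trial says about lasting relief rests on these two ratings.

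**Working it through.** No sample size, power or alpha figure bears on this point. The check is to set the procedures in order and ask, for each outcome, what the evaluator knows when it is collected.

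1. **Baseline.** The evaluator collects all outcomes before treatment (2.6). There is no guess to hear.
2. **Treatment.** Ten weekday sessions (2.6, 2.7), given by the therapist, who knows the allocation (2.20).
3. **Post-treatment evaluation.** The evaluator collects the primary outcome and the secondary outcomes (2.8.1, 2.8.2). The blinding check comes only after this evaluation is finished (2.21), so the evaluator has still heard no guess.
4. **Evaluator's guess, then patient's guess** (2.21). This order is sound in one respect: the evaluator commits before hearing the patient, so the evaluator's own answer is not contaminated. From here on, however, the evaluator knows the patient's belief about both therapies.
5. **Telephone call 6 weeks after randomization** (2.6, 2.8.2). The evaluator collects pain intensity and GPE with that knowledge.

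**Outcomes exposed.** At 6 weeks, 2 of 2. At post-treatment, none, including the primary outcome.

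**Patients exposed.** All those reached at 6 weeks: at most 144, or 144 × (1 − 0.15) = 122.4, about 122, if the full 15% loss allowed for in section 2.22 occurs.

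**Interval.** Ten weekday sessions take 10 / 5 = 2 weeks. If they begin at about randomization (an assumption, since no start interval is given), the guess is heard about 6 − 2 = 4 weeks before the call.

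**Is a second assessor described?** No. Section 2.6 has one evaluator role, and that role is named both for asking the guess and for making the call.

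**Is allocation disclosed to the patient or evaluator?** No section says so. Only the therapist is described as opening the envelope.

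**The case against.** The case on the other side is substantial, and most of it stands.

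*Blinding does not stop at the end of treatment.* A reader might infer from "Patient and evaluator will be blinded throughout the treatment" that the blind is planned to lapse about 4 weeks before the call. The documents do not support this. The abstract and section 2.1 state patient and evaluator blinding with no end date. Taken literally, the sentence would also leave out the post-treatment evaluation that holds the primary outcome, yet section 2.21 tests the blind after that evaluation and so presumes it still holds. The sentence is loosely worded and needs aligning.

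*The 6-week outcomes are not unprotected.* A reader might infer that too. But a guess is not the allocation, and it may be wrong or a don't-know. The sham controls, concealed allocation and separation of therapist from evaluator remain in place, and section 2.23 has a blinded analyst. The TENS sham was designed to help blinding, and the question in section 2.21 is categorical and does not ask about sensation. Protection is weakened but not lost. Analyst blinding, however, cannot remove bias that enters during the interview.

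*Patient expectation arises elsewhere.* If patients notice a difference, they do so during the sessions, whoever hears the guess. This also stands: the point concerns only the evaluator's knowledge.

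*Asking at the end of treatment is defensible.* Agreed. Recall of the sessions is fresh, and the answer is not yet coloured by how long relief lasted. The timing can stay; only who learns the answer needs to change.

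None of this answers the remaining fact that the person collecting the 6-week ratings has been told each patient's belief, and need not have been.

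**Conclusion.** The point holds as a minor, cheap improvement. The stated sequence gives the evaluator each patient's belief about both therapies before the same evaluator collects pain and GPE at 6 weeks. This weakens evaluator blinding for two secondary outcomes, the only ones that speak to durability. It does not touch the primary outcome, and no unblinding is planned or described.

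No magnitude can be given. It would be tempting to posit a shift in pain score and express it as a share of the 2.3-point planning difference in section 2.22. Nothing in the documents anchors such a shift, and a general expectation effect is not the same as the added effect of an evaluator having heard a guess.

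The conclusion assumes that the evaluator in sections 2.6 and 2.21 is one and the same person, as the two-researcher description implies. If a different assessor makes the calls and has no access to the recorded guesses, the point falls away, and the protocol should say so.

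**What to change.** **Section 2.21.** Keep the blinding check at the post-treatment visit and keep the evaluator's own guess as it is. Have the patient answer the two questions on a self-completed form, seal it, and hand it in. The evaluator does not open it until that patient's 6-week data are complete.

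**Section 2.20.** Replace the sentence on duration with one saying that patient and evaluator remain blinded to allocation until the 6-week call has been completed. This aligns it with the abstract and section 2.1.

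**Cost.** One sheet of paper and an envelope per patient, and somewhere to keep them. No extra staff or visit is needed, and patients already complete a self-administered questionnaire at this visit (section 2.16).

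**Limits.** The form closes only the evaluator route. It does not remove expectation that patients form during the sessions, nor any effect on the patient of being asked the question. Asking at the end of the 6-week call, after both ratings, would avoid that last effect, but recall would be weaker and the guess more coloured by how well relief had lasted. The sealed form is the better trade.

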### Study blinding assessment

2.21

Assessment of the effectiveness of blinding will be performed after the conclusion of the posttreatment evaluation. The evaluator will answer whether he thinks that the application of photobiomodulation and electrical current was real, placebo, or he does not know. After that, the evaluator will ask the patient: “Do you think that the application of photobiomodulation was real, placebo, or did not know?” and “Do you think that the application of electrical current was real, placebo, or do you not know?” Their responses will be recorded and used to gauge the adequacy of subject and investigator blinding.

### Sample size

2.22

The sample size of the study was performed based on the pain intensity outcome (as measured by the pain numerical rating scale) with mean difference of 2.3 points and an estimated standard deviation of 2.76 points.^[13]^ Statistical power of 80% was considered with an alpha of 5% and possible sample loss of up to 15%. Accordingly, a total of 144 patients will be required for the study. The sample calculation was performed using the Minitab software, version 17, (Minitab, Inc., PA).

### Statistical analysis

2.23

All study-related information will be stored securely at the study site. All participant information will be stored in locked file cabinets in areas with limited access. The principles of intention-to-treat analysis will be used for the statistical analysis.^[50]^ The Shapiro-Wilk test will be used to verify the normality of the data. If the data present a normal distribution, a parametric test will be used. Otherwise, a nonparametric test will be used. The level of significance adopted will be *P* < .05. Data analysis will be performed using the SPSS software version 17 (SPSS, Inc., IL) by a researcher blinded to the division of the groups.

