### Inclusion criteria

2.4

Patients with non-specific chronic neck pain, defined as pain or discomfort in the posterior cervical region between the superior nuchal line and the first thoracic spinous process and/or shoulder girdle;Neck pain for at least 3 months;Neck disability index (NDI) score of 5 points or higher;Numeric rating scale (NRS) score of ≥3 for pain intensity;Aged between 18 and 65 years;Men and women.

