#### Primary outcome

2.8.1

Pain intensity after treatment (10 sessions).

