### Pain intensity—numeric rating scale

2.9

Pain intensity will be evaluated using a NRS, which is a simple and easy-to-use measuring scale that consists of a sequence of numbers from 0 to 10, in which 0 represents “no pain” and 10 represents “the worst pain imaginable.” Then, patients rate their pain based on these parameters.^[28]^ The pain evaluation will be carried out verbally with the patient reporting the pain intensity.

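### A Shapiro-Wilk result on unspecified data picks the unnamed test for the primary outcome, and so decides whether the trial reports the mean difference it was sized on; one model should be fixed instead

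*Protocol article*

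**What the plan says.** The Statistical analysis section (2.23) of the protocol article gives one rule for all outcomes. "The Shapiro-Wilk test will be used to verify the normality of the data", and then: "If the data present a normal distribution, a parametric test will be used. Otherwise, a nonparametric test will be used". It does not define the data to be tested, name either test or mention covariates. It does state intention to treat, a 5% level and an analyst blinded to group.

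Other sections bear on the rule:
- The primary outcome is pain intensity after the ten sessions, on a scale that "consists of a sequence of numbers from 0 to 10" (2.9).
- Entry requires "Numeric rating scale (NRS) score of ≥3 for pain intensity" (2.4).
- Baseline pain will be on file: "The patients will be evaluated before the treatment, after the treatment (10 sessions) and 6 weeks after randomization" (2.6).
- Sex is the stratification factor: "Patients will be stratified by sex to ensure equal numbers of women and men in each group" (2.20).
- The sample size (2.22) rests on a mean difference of 2.3 points with SD 2.76.

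**The concern.** A preliminary normality test makes the primary analysis depend on the outcome data. The two branches differ in more than technique. A t-test, ANOVA or linear model estimates a difference in mean points, the quantity used to size the trial. The usual nonparametric choices, Kruskal-Wallis or Mann-Whitney, compare ranks. They also make no use of baseline pain or of the stratification factor.

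Because the tested data are undefined, the same dataset could lead to either branch, depending on whether the analyst checks each arm, all scores together or the residuals. At stake are a primary effect measure that is fixed in advance and the precision available from a baseline score that is already collected.

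**Working it through.** **Inputs.** From the article: 0-10 scale, 36 per arm, difference 2.3, SD 2.76, 15% loss. After loss, 36 × 0.85 = 30.6, so about 30-31 per arm. Assumed, because the article gives no figure: post-treatment arm means and the baseline-post correlation ρ.

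**The plan's own figure.** The stated total of 144 does not reproduce.
- Two-sample normal approximation: 2 × (1.96 + 0.842)² × 2.76² / 2.3² = 22.6, so 23 per arm; 23 / 0.85 gives 28, and 4 × 28 = 112.
- Four-arm ANOVA with a maximum difference of 2.3: 33 per arm; 33 / 0.85 gives 39, and 4 × 39 = 156.

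That is a separate matter. The point here needs only the 2.3 and the 2.76.

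**Step 1: how often the gate switches.** Normal scores were rounded and clipped to 0-10, then tested with Shapiro-Wilk at 5%. With 36 per arm and SD 2.76:

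| Common arm mean | One given arm rejects | At least one of four |
|---|---|---|
| 5 | 14% | 46% |
| 4 | 33% | 80% |
| 3 | 77% | >99% |
| 2 | 99% | about 100% |

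The last column is 1 − (1 − p)⁴; for mean 4, 1 − 0.668⁴ = 0.80.

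With arm means 2.3 points apart at the extremes, 36 per arm:

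| Arm means | SD | At least one arm | Residuals | All scores pooled |
|---|---|---|---|---|
| 2.7 to 5.0 | 2.76 | 96% | 78% | about 100% |
| 3.85 to 6.15 | 2.76 | 73% | 45% | about 100% |
| mid-scale | 2.0 | 66% | 23% | about 100% |

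With 31 per arm the rates are lower: roughly 60-90% for at least one arm and 30-75% for residuals at SD 2.76, and about 20% for residuals at SD 2.0. The choice among arms, residuals and pooled scores, which the article leaves open, can matter as much as the data.

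**Step 2: what the switch costs in power.** Simulated, 36 per arm, means 2.7 to 5.0, ρ = 0.5 (ρ affects only the ANCOVA line):
- ANOVA: 82.8%
- Kruskal-Wallis: 81.6%
- Shapiro-Wilk, then the chosen test: 81.8%
- ANCOVA on baseline pain: 92.8%

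The gate costs 82.8 − 81.8 = 1.0 point. For two arms, the t-test has 93.1% and Mann-Whitney 92.0%. Across the scenarios examined, the rank test costs about 1-3 points.

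**Step 3: type I error.** With all means equal, the two-stage procedure rejected in 5.6% of 2,000 trials. The simulation standard error is √(0.05 × 0.95 / 2000) = 0.5 points, so this is compatible with 5%.

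**Step 4: what baseline adjustment adds.** Adjustment replaces the SD by 2.76 × √(1 − ρ²). The four-arm F test has noncentrality n × (2.3² / 2) / SD². For n = 36 and ρ = 0 this is 36 × 2.645 / 7.6176 = 12.5; for ρ = 0.5 it is 12.5 / 0.75 = 16.7.

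| ρ (assumed) | Power, 36 per arm | Power, 30 per arm |
|---|---|---|
| 0 | 84.5% | 76.4% |
| 0.3 | 88.0% | 80.7% |
| 0.5 | 93.7% | 88.2% |
| 0.7 | 99.1% | 97.3% |

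At 36 per arm the gain is 3.5 points for ρ = 0.3 and 9.2 for ρ = 0.5. The simulated gains are about 3 and 10. At 30 per arm the formula gives 4.3 and 11.8.

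**The case against.** The best defence is that this is a condensed article with no analysis plan shown, and that test names and covariates are commonly left to such a plan. For covariates that stands. A reader might infer that the primary analysis ignores baseline pain and sex, but the article is silent on adjustment and does not rule it out; its parametric test could be an ANCOVA. The defence does not cover the gate, which is a stated rule. An analysis plan that fixed one primary model would contradict it.

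A reader might also infer that the switch will usually happen. That holds if every arm must pass and post-treatment means are about 4 or lower, or if all scores are pooled. It does not hold in general for residuals with mid-scale means, and the article gives no expected post-treatment means.

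A third tempting reading is that the gate forces a much weaker test. Setting an unadjusted Mann-Whitney beside an ANCOVA seems to show this, but most of that gap is baseline adjustment. In a two-arm simulation (31 per arm, assumed difference 1.5, SD 2.76, ρ = 0.5), power was 55.6% for the t-test, 53.9% for Mann-Whitney and 64.7% for ANCOVA. Nor are rank methods as a class unable to use covariates or strata. Quade's rank ANCOVA reached 62.2% in the same setting, van Elteren's test is stratified, and aligned-rank procedures address interactions. The limits apply to plain Kruskal-Wallis and Mann-Whitney, which are the usual choices but are not named in the article.

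Finally, the analyst is blinded to group. That limits the chance to favour an arm, but it does not settle which effect measure is reported.

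**Conclusion.** The point holds as a badly fixed rule. A Shapiro-Wilk result on undefined data selects between two unnamed tests, and with it the effect measure for the primary outcome. On this scale with SD 2.76 a switch is a real possibility; its probability depends on the assumed arm means and on which data are tested.

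The demonstrated statistical harm of the gate itself is small: about 1-3 power points and no visible type I inflation. The main reasons to change it are to fix the effect measure in advance and to secure the gain from baseline adjustment. That gain is about 3 points at ρ = 0.3 and 9-10 at ρ = 0.5 with SD 2.76, nothing at ρ = 0, and it rests on a correlation the article does not give. The benefit of adjusting for sex cannot be computed from the article. This should be fixed, but it does not undermine the trial.

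**What to change.** Delete the normality gate for the primary outcome and name one primary analysis: a linear model (ANCOVA) of post-treatment NRS on treatment group, baseline NRS and sex, in all randomised patients, reporting adjusted mean differences with 95% confidence intervals. With 30-36 patients per arm on a bounded score, such a model does not need normally distributed raw data. Keep a rank-based or bootstrap analysis as a sensitivity check only. If an analysis plan already names such a model, bring the protocol text into line with it.

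The cost is wording. Baseline pain and sex are already collected, and the planned software fits the model. The change should be made before unblinding.
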